### Sample size {14}

The sample size was calculated for a randomized single-factor ANOVA design with 3 groups without clustering, assuming 30 days of illness (standard deviation of 10 days) during 180 days of follow-up in the control group and a reduction by 4 days for the high-intensity intervention (effect size of Cohen’s *d* = 0.4) and a reduction by 1 day in the medium intensity group. Such reduction was deemed by occupational health physicians as well as general practitioners as clinically highly relevant. Compared to the control group, a power of 80%, a type 1 error probability of less than 5%, and a dropout rate of 25% result in a required sample size or *N* = 151 per group. Thus, we aim to include at least *N* = 453 patients. In order to be able to exclude possible correlations due to socio-demographic variables corresponding to the location of participating practices (in particular rural doctors versus urban infrastructure), the target size is an increased sample size of 600 patients in total (*N* = 200 patients per study arm).

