#### Plans to promote participant retention and complete follow-up {18b}

Participant retention plans are consistent with the strategies to improve adherence to interventions described in {11c}. Full follow-up is usually ensured by adherence to the GP, unless patients generally change their GP. As many of the planned outcomes as possible are collected for all participants, including those who drop out.

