### Statistical methods

#### Statistical methods for primary and secondary outcomes {20a}

Generalized linear models will be used to compare the distribution of primary outcomes (sick leave days) in the randomization groups. Link function will be determined based on the observed sample distribution (we expect Poisson or Negative Binomial distribution). Secondary outcomes will be analyzed by Repeated Measurements Analysis of Variance and Mixed Models for Change analysis. Longitudinal response curves will be visualized by graphs showing the marginal estimates in the randomization groups. All statistical analysis will be conducted using the software package STATA (StataCorp. 2019. Stata Statistical Software: Release 16. College Station, TX: StataCorp LLC).

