#### Methods in analysis to handle protocol non-adherence and any statistical methods to handle missing data {20c}

Statistical analysis will be conducted using complete case analysis and as a sensitivity analysis using imputed data based on a multiple imputation algorithm. If the distribution of the observed missing pattern is at random, the core model will be based on the imputed data.

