At the same time, there is a risk of bias, if only particularly motivated GPs who are aware of the problem enroll patients. Patients of GPs, who do not accept Long COVID as an independent clinical condition or who do not consider it to be of significance, will not be given access.

There are numerous dropout risks for successfully enrolled patients. Due to the digital-only form of the program, which offers advantages for accessibility and scalability, there is the disadvantage of a lack of human support and contact. This applies in particular to the control and the moderate intensity intervention group, which have no regular human support, meaning that an impending drop-out cannot be recognized or counteracted.

It is also possible for participants to drop out silently by simply not logging in anymore. Although the LMS sends automatic reminder emails, these also lack the option of responding individually to the respective reasons for leaving.

For the high-intensity intervention group, there is a specific dropout risk due to the initial waiting period. After enrolment, registration in the LMS, and randomization, participants in this group must first select a webinar group. Once this has been done, the first webinar and therefore access to the platform content only starts when the required group size has been reached. If only a few participants are enrolled or randomly assigned to the high-intensity intervention group in a given period, these waiting times can quickly become quite long. This could lead to a large number of dropouts. It may therefore be necessary to flexibly adjust the minimum group size to the current enrollment rate in order to counteract mass dropout.

Overall, the structure of the trial may be very sensitive to possible deviations from the planned sample size and predicted adherence rates.

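### Secondary outcomes have two analysis methods with no lead and a complete-case default; a mixed model on all available data should lead, and the missing-data rule should be changed to match

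*Protocol article*

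**What the plan says.** Section {20a} on statistical methods: "Secondary outcomes will be analyzed by Repeated Measurements Analysis of Variance and Mixed Models for Change analysis". Neither method is given precedence, and no outcome is assigned to one or the other.

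Section {20c} on missing data sets a general rule: "Statistical analysis will be conducted using complete case analysis and as a sensitivity analysis using imputed data based on a multiple imputation algorithm". It then adds a switch: "If the distribution of the observed missing pattern is at random, the core model will be based on the imputed data". It does not say whether the core model includes the models for secondary outcomes.

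Section {18b} on retention: "As many of the planned outcomes as possible are collected for all participants, including those who drop out".

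On dropout, the sample size section {14} plans for "a dropout rate of 25" per cent. The section on possible conceptual risks says: "It is also possible for participants to drop out silently by simply not logging in anymore". It gives different causes by arm. On the lack of human contact in a digital-only programme: "This applies in particular to the control and the moderate intensity intervention group, which have no regular human support". On waiting for a webinar group to fill: "For the high-intensity intervention group, there is a specific dropout risk due to the initial waiting period".

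The outcomes section {12} places the main questionnaires at T0 (enrolment), T2 (3 months) and T3 (6 months). Section {18a} collects all of them inside the learning platform.

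**The concern.** A participant who stops logging in stops supplying exactly these outcomes. A classical repeated-measures ANOVA needs T0, T2 and T3 all present, so under a complete-case rule a participant who answered T0 and T2 but not T3 contributes nothing. That wastes data which section {18b} sets out to collect. It can also distort the arm comparison if the people who leave differ in health between arms.

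The second issue is choice. Two methods, each on complete-case or imputed data, give up to 2 × 2 = 4 results per scale. The rule for moving to imputed data depends on a judgement made after the data are seen, and section {17a} says the analysts are generally not blinded. The plan does not fix in advance which result is the trial's answer on, for example, depression or quality of life.

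**Working it through.** **1. The plan's own figure, to place the 25%.** Section {14} assumes a one-way ANOVA with means 30, 26 and 29 days and SD 10. The grand mean is 28.33, and the squared deviations sum to 2.78 + 5.44 + 0.44 = 8.67. With n = 113 per group, the noncentrality is 113 × 8.67/100 = 9.79 on 2 and 336 degrees of freedom, which gives 80.3% power at 5%. Dividing by 1 − 0.25 gives 113/0.75 = 150.7, so 151. The published figure is reproduced. The 25% therefore belongs to the sick-leave sample size; no rate is given for the questionnaires.

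**2. Participants left, if 25% lack T3.** Per arm: 200 × 0.75 = 150, or 151 × 0.75 = 113 at the minimum size. In total, 600 × 0.75 = 450.

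**3. Precision under random loss at T3, in closed form.** Let R² be the share of variance of the change T3 − T0 explained by T0 and T2, and d the fraction missing T3. Then

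variance(complete case) / variance(all available data) = 1/(1 − d·R²).

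The documents give no correlations, so four sets are assumed, with d = 0.25:

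| Correlations T0–T2, T2–T3, T0–T3 | R² | Ratio by formula | Ratio by simulation |
|---|---|---|---|
| 0.5, 0.5, 0.5 | 0.333 | 1.09 | 1.09 |
| 0.7, 0.7, 0.7 | 0.294 | 1.08 | 1.11 |
| 0.5, 0.7, 0.45 | 0.548 | 1.16 | 1.15 |
| 0.5, 0.8, 0.3 | 0.752 | 1.23 | 1.22 |

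**4. Other dropout patterns, by simulation.** Two arms of 200, true effect −0.3 SD, 400 to 500 runs per scenario. Dropout at T3 is 25% and depends on the T2 score with the slopes shown for the two arms. The last column has 12.5% missing at random at each of T2 and T3, which leaves 0.875² = 77% complete. Each cell gives the variance ratio, then the complete-case bias in SD units (Monte Carlo error 0.005 to 0.007).

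| Correlations | Random | Same slope (1, 1) | One arm only (1.5, 0) | Opposite (1, −1) | 12.5% per visit |
|---|---|---|---|---|---|
| 0.5, 0.5, 0.5 | 1.09; 0.008 | 1.14; 0.002 | 1.09; 0.007 | 1.12; 0.004 | 1.32; −0.006 |
| 0.7, 0.7, 0.7 | 1.11; −0.001 | 1.09; 0.000 | 1.08; 0.009 | 1.06; 0.000 | 1.17; −0.004 |
| 0.5, 0.7, 0.45 | 1.15; 0.004 | 1.26; 0.009 | 1.14; 0.065 | 1.11; 0.081 | 1.25; −0.004 |
| 0.5, 0.8, 0.3 | 1.22; −0.001 | 1.17; 0.016 | 1.32; 0.103 | 1.13; 0.134 | 1.29; 0.004 |

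The mixed model (unstructured covariance) had bias of at most 0.01 SD in every cell.

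**5. Why the bias comes and goes.** With unit variances, the change T3 − T0 regresses on T2 with slope r(T2,T3) − r(T0,T2). For the four sets this is 0, 0, 0.7 − 0.5 = 0.2 and 0.8 − 0.5 = 0.3. Selecting on T2 shifts the mean change only when this slope is not zero, and it shifts the arm contrast only when the selection differs by arm. In the worst cell the estimate moves from −0.30 to about −0.30 + 0.134 = −0.17. The sign depends on which arm loses which participants.

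**The case against.** The strongest reply is that section {20c} already deals with missing data. If missingness is judged to be at random, the core model uses imputed data and nobody is dropped; that is also the setting in which a mixed model does best. If complete case is applied throughout, the mixed model loses the same people as the ANOVA. Both points stand. A reader might infer from {20a} that the ANOVA necessarily drops everyone with a missing visit. The documents do not support that: it follows only under the complete-case default and a classical data layout. An ANOVA on long-format data can keep partial records, although in the same simulations that version was still biased by up to about 0.1 SD in some arm-dependent scenarios. The switch in {20c} does not resolve the matter, because observed data cannot show that missingness is at random.

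Second, the bias needs dropout that depends on scores differently by arm. The article gives arm-specific causes (waiting, lack of contact) but never says that dropout depends on scores. A reader might also apply the 25% separately to T2 and T3 and conclude that 1 − 0.75² = 44% would be lost. The article states a single rate, for the primary outcome, so that figure is not supported.

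Third, lead method, covariance structure and lead time point are often left to the analysis plan. Their absence alone would be no finding. What remains is what the article does state: a weaker method placed level with a better one, under a complete-case default.

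**Conclusion.** The point holds as a modest, inexpensive improvement to the secondary analyses. Sections {20a} and {20c} together allow a completers-only analysis to stand as the result for these scales. Under the assumed correlations (0.3 to 0.8) and about 25% dropout, that analysis has 6% to 32% more variance than a mixed model on all available data. Its bias is 0 to 0.02 SD when dropout is random or depends on earlier scores equally in both arms, and 0 to 0.13 SD on a true 0.3 SD effect when the dependence differs by arm.

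The correlations, the dropout slopes and the use of 25% for the questionnaires are assumptions. It would go too far to say that the secondary results will be biased, or that the fault lies in the ANOVA alone: the complete-case rule matters as much.

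**What to change.** In {20a}: for the scored scales collected at T0, T2 and T3 (SF-12, PHQ-9, GAD-7, CBI, ESSI, FFB-MOT, sleep quality), name as lead analysis a linear mixed model on all available T2 and T3 values. Include arm, visit and arm-by-visit, adjusted for the T0 value and the stratification factors. Name the T3 arm contrast as the lead estimate. Delete repeated-measures ANOVA or label it supportive.

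In {20c}: state that the complete-case restriction does not apply to this model, and that the choice of analysis does not depend on a judgement from the data that missingness is at random. Keep multiple imputation as a sensitivity analysis, and include participants with no follow-up value, whom the mixed model leaves out.

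Outcomes that section {18a} does not score (PHQ-15, CMDQ, adapted WAI, breathlessness) and the weekly WHO-5, which is collected only at T1, keep their own analyses.

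Cost: a change of wording in two sections that must be made together. Mixed models are already planned and available in the named software. No data collection or sample size changes.

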#### Interim analyses {21b}

Interim analyses will only take place in the form of the regular monitoring of participation numbers by the study management team and will not constitute a study termination.

The only defined criterion for study termination is data protection incidents (especially if there is a risk of recurrence or expansion). The final decision on study termination is then made by the primary sponsor.

#### Methods for additional analyses (e.g., subgroup analyses) {20b}

Subgroup analyses will be conducted repeating the efficacy analyses in subgroups of the study population defined by patient-specific variables. Subgroup analyses focus on elucidating observed heterogeneity of effect sizes rather than testing for statistical significance, as the sample size of the study has been defined to achieve sufficient power for the main analysis. Subgroup analyses have only exploratory objectives and nature; therefore, we refrain from adjustment for multiple comparisons. Rather than reporting statistical inference test results, we will report observed effect sizes and related confidence intervals without adjustment for multiple testing.

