**Discussion:**

If one of the two interventions is superior to providing information alone, MiLoCoDaS would provide the starting point for a rapidly scalable digital intervention for the frequent and currently underserved patient group with mild to moderate impairment from Long COVID. Several caveats pertain to the heterogeneity of Long COVID manifestation and duration prior to inclusion. It is conceivable that the possible effect of the intervention may differ across subgroups. Therefore, a priori defined secondary analysis will be conducted.

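### Subgroup analyses aim at heterogeneity of effect but plan only separate within-subgroup results, so the between-subgroup difference and its uncertainty are not among the planned outputs

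*Protocol article*

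**What the plan says.** Section {20b} of the protocol article gives the method: "Subgroup analyses will be conducted repeating the efficacy analyses in subgroups of the study population defined by patient-specific variables". It gives the purpose: "Subgroup analyses focus on elucidating observed heterogeneity of effect sizes rather than testing for statistical significance". On status it says: "Subgroup analyses have only exploratory objectives and nature; therefore, we refrain from adjustment for multiple comparisons". On output it says that "we will report observed effect sizes and related confidence intervals without adjustment for multiple testing".

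The analysis to be repeated is described in section {20a}: "Generalized linear models will be used to compare the distribution of primary outcomes (sick leave days) in the randomization groups". That section names no arm-by-subgroup term, and no other section names a between-subgroup contrast or an interval for one.

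The Discussion part of the Abstract explains why subgroups are examined: "It is conceivable that the possible effect of the intervention may differ across subgroups". It presents the secondary analysis, described there as defined in advance, as the response.

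**The concern.** The aim and the method in {20b} do not meet. An analysis run separately in each subgroup answers whether the intervention works in that subgroup. Heterogeneity asks whether the effect differs between subgroups, which is a contrast of the two effects with its own, larger standard error. The plan would print the components and leave out the quantity it says it is studying.

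The article returns to effect modification several times. The burnout inventory is included partly to detect a differing intervention effect by burnout score. Baseline items are collected to allow fine-grained subgroup analyses. The Limitations section calls sample heterogeneity a fundamental challenge. At stake is how far a reader can judge an apparent difference between subgroups. Two intervals side by side make the comparison look more precise than it is.

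**Working it through.** **Inputs from the Sample size section {14}.** The design basis is: "The sample size was calculated for a randomized single-factor ANOVA design with 3 groups without clustering". Controls are taken to have a mean of 30 sick days with an SD of 10 over the 180 days. The high-intensity arm is assumed to reduce sick leave by 4 days (d = 0.4) and the medium-intensity arm by 1 day. Power is 80%, type I error 5%, dropout 25%, and the target is 200 per arm. (The Abstract quotes an effect of 0.3; the figures below use {14}.)

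**Assumptions not in the article.** A binary subgroup factor split 50:50, 95% intervals, and the same true effect in both subgroups. The normal scale follows {14}; the planned analysis is a count model.

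**Reproducing the plan's figure.** Means 30, 29 and 26 have grand mean 28.33. The sum of squared deviations is 2.78 + 0.44 + 5.44 = 8.67. The noncentrality is n × 8.67/100. At n = 113 per group the one-way ANOVA F test has 80.3% power, and 113/0.75 = 150.7, which rounds up to 151. This matches the article, so its inputs can be used.

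**Precision, high intensity versus control.** Evaluable per arm: 200 with no loss, or 200 × 0.75 = 150. Half of each gives n = 100 or 75 per arm per subgroup.

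- SE within a subgroup = 10 × √(2/n)
- SE of the difference between subgroups = √2 × that SE
- 95% half-width = 1.96 × SE

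| n per arm per half | SE within | Half-width within | SE of difference | Half-width of difference |
|---|---|---|---|---|
| 100 | 1.41 | 2.8 days | 2.00 | 3.9 days |
| 75 | 1.63 | 3.2 days | 2.31 | 4.5 days |

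At n = 75 the interval for the difference extends further on each side than the whole 4-day design effect.

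**Chance that exactly one of the two intervals excludes zero.** With power p in each half this is 2p(1 − p).

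- 4-day effect, n = 100: p = 0.804, so 2 × 0.804 × 0.196 = 0.32.
- 4-day effect, n = 75: p = 0.682, so 2 × 0.682 × 0.318 = 0.43.
- 1-day effect (the medium-intensity assumption): about 0.19 at n = 100 and 0.17 at n = 75.
- No effect: 2 × 0.05 × 0.95 = 0.095.

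A simulation of 200,000 trials using the normal approximation gave 31% and 43% for the two 4-day cases. With 150 evaluable per arm, an uneven split raises the figure, to 52% at 30:70 and 62% at 20:80.

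**Without reference to zero.** At 150 per arm and an even split, two subgroups with the same true effect differ in their point estimates by 2.31 × √(2/π) = 1.8 days on average. They differ by 2 days or more in 39% of trials. This does not depend on the size of the common effect.

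**With the contrast reported.** When the true effects are equal, the 95% interval for the difference excludes zero in 5% of trials per factor (simulated: 5.0%). Power to detect a true 4-day difference at 150 per arm, even split: 4/2.31 = 1.73, and Φ(1.73 − 1.96) = 0.41.

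**The case against.** The strongest objection is that {20b} rejects the reading that produces the 43% and 32%. It disclaims significance testing, labels the analyses exploratory and promises effect sizes with intervals. Those percentages therefore describe what a reader might do with the output, not an inference rule in the plan. This stands. It limits the weight of the point, but the exploratory label and the absence of tests deal with multiplicity and not with which quantity is estimated.

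Second, subgroups that do not overlap, each reported with an interval, carry enough information for the difference and its SE to be worked out. This also stands. It would be wrong to infer that heterogeneity cannot be learned from the planned results; what is missing is the explicit contrast.

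Third, this is a journal article, and a separate analysis plan may add a contrast. That is possible. Still, {20b} states a method as well as an aim, and the stated method does not deliver the aim.

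A reader might also infer that spurious subgroup differences will steer later tailoring of the programme. The article does not say so. The tailoring described in Limitations is towards occupational reintegration and is not tied to subgroup results. Type of employment appears as a randomisation stratum, not as a stated source of heterogeneity.

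**Conclusion.** The point holds as a mismatch between aim and planned output: the plan wants to describe heterogeneity of effect and does not include the between-subgroup difference or its interval. The primary comparison is unaffected.

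The size is best read from the precision figures. With 150 evaluable per arm and an even split, the difference between halves is known to about ±4.5 days while each subgroup interval shows ±3.2. These rest on an SD of 10, normal outcomes and an even split; none of the splits used is a planned one.

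A reader might conclude that the plan will often show false subgroup differences. That needs qualifying. The 32 to 43% range requires a real common 4-day effect, the high-intensity contrast, an even split and intervals read against zero. It falls to 17 to 19% for a 1-day effect and to 9.5% with no effect, and rises with uneven splits.

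**What to change.** In {20b}, or in the analysis plan, replace the repeated within-subgroup analyses with the following. For each subgroup factor listed in advance, including the four stratification factors (age, gender, type of employment, disease status), fit the primary model on all participants with arm-by-subgroup interaction terms. Report each interaction with its 95% CI, as a ratio of rate ratios or a difference in days, with the scale named in advance. Beside it, show the subgroup effects from the same model. Keep the exploratory label, and add neither tests nor multiplicity adjustment.

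The cost is a sentence or two of text and, with three arms, (3 − 1) × (2 − 1) = 2 interaction parameters per binary factor. Conduct, data collection and sample size do not change. The drawback is that the interaction intervals will be wide: power is only about 41% for a 4-day difference between halves at 150 evaluable per arm, 35% at a 30:70 split and 28% at 20:80. The report should state this limited precision.

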#### Methods in analysis to handle protocol non-adherence and any statistical methods to handle missing data {20c}

Statistical analysis will be conducted using complete case analysis and as a sensitivity analysis using imputed data based on a multiple imputation algorithm. If the distribution of the observed missing pattern is at random, the core model will be based on the imputed data.

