#### Criteria for discontinuing or modifying allocated interventions {11b}

No changes to the assigned interventions are intended. However, all exercises shown in the program are voluntary and can be done or skipped by the participants individually. Thus, less intervention components deemed by the participant to be less beneficial can be excluded individually.

The attending GP may exclude participants from further participation at any time for medical reasons. The assessment of reasons (e.g., worsening disease) is the exclusive responsibility of the GP.

Participants themselves can terminate their participation at any time by revoking their consent.

Any of the following situations during the study period will also lead to discontinuation:Hospitalization due to COVID-19 or post-COVID-19-disease.Referral to long-term specialist outpatient treatment due to COVID-19 or post-COVID-19 disease.

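### Section {20c} lets a condition that observed data cannot establish decide whether complete-case or imputed data give the core result

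*Protocol article*

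**What the plan says.** Section {20c} of the protocol article first ranks the two approaches: "Statistical analysis will be conducted using complete case analysis and as a sensitivity analysis using imputed data based on a multiple imputation algorithm". The next sentence can reverse that ranking: "If the distribution of the observed missing pattern is at random, the core model will be based on the imputed data". It gives no test, threshold, decision-maker or time point for the judgement.

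Four other sections bear on it:

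- **Blinding {17a}:** study management and data analysts are generally not blinded. They have no direct access to participant data during the trial, and evaluation follows study completion.
- **Statistical methods {20a}:** the link function for sick-leave days is also to be chosen from the observed distribution.
- **Outcome collection {18a}:** the GP totals sick-leave and reintegration days from routine records for each participant she enrolled, over six months from registration.
- **Retention {18b}:** "As many of the planned outcomes as possible are collected for all participants, including those who drop out". The section expects follow-up through the GP to be usually complete unless the patient changes GP.

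**The concern.** Missing at random and missing not at random differ only in how loss depends on the unobserved outcomes. Two mechanisms can leave the same observed pattern and still differ on this point, so the condition in {20c} cannot be verified from that pattern. What can partly be checked is whether loss is unrelated to observed variables, that is, completely at random. In that case complete cases are unbiased and imputation is needed least. On neither reading does the condition do the job given to it.

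The other branch is weak as well. If loss is judged not at random, the core model stays with complete cases, which are generally not valid when loss depends on the outcome.

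At stake is which of two results is reported as the trial's main finding. The decision falls after the data are in, without a written criterion, to people who may know the allocation.

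**Working it through.** **The plan's own figure.** Section {14} states: "The sample size was calculated for a randomized single-factor ANOVA design with 3 groups without clustering". Its inputs are a control mean of 30 days with SD 10, 4 days fewer in the high-intensity arm and 1 day fewer in the medium arm.

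- The means are 30, 29 and 26, with grand mean 28.33. The squared deviations sum to 2.78 + 0.44 + 5.44 = 8.67.
- Noncentrality with n per group is n × 8.67/100. At n = 113 it is 9.79, and the F test at 5% has power 80.3%.
- Allowing for 25% dropout, 113/0.75 = 150.7, so 151 per group. The stated figure is reproduced.

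**What the switch changes.** Take the worst case, in which every one of the planned 25% dropouts lacks the primary outcome. At 600 enrolled, the complete-case core set is 600 × 0.75 = 450 (150 per arm, ANOVA power 90.6%). The imputed core set is 600. Power is adequate either way, so the issue is which analysis is primary, not the sample size.

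**Can the observed pattern decide?** An illustrative simulation assumed two arms of 151, no true effect, a normal outcome with SD 10, one covariate correlated 0.5 with the outcome, roughly 25% missing and 3,000 runs. Loss was declared at random when it was associated with the covariate at p < 0.05 in either arm. Complete cases were compared without adjustment.

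| Assumed loss | Declared at random | Complete-case: bias, type I error | Imputation: bias, type I error | Switching: bias, type I error |
|---|---|---|---|---|
| Completely at random | 10% | 0.0 days, 5.1% | 0.0 days, 5.0% | 0.0 days, 4.9% |
| At random, opposite by arm | 100% | −1.8 days, 28% | 0.0 days, 4.3% | 0.0 days, 4.3% |
| Not at random, opposite by arm | 74% | −3.7 days, 83% | −2.8 days, 62% | −3.0 days, 66% |

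Two things follow.

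- With loss that was truly not at random, the check still declared it at random in 74% of runs.
- The missing criterion matters. Someone could equally read the sentence as meaning that no association implies random loss and therefore imputation. In the second row that reading keeps complete cases in essentially every run, with bias −1.8 days instead of 0. The same sentence supports opposite choices.

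These mechanisms are assumed and strong. They show what the rule cannot detect and are not estimates for this trial.

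**Size under a stated assumption.** Suppose there is no true effect, both arms have mean 30, and lost participants average L days. With a fraction q lost, the complete-case mean is (30 − qL)/(1 − q).

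- L = 45, q = 0.10: (30 − 4.5)/0.90 = 28.33.
- L = 45, q = 0.05: (30 − 2.25)/0.95 = 29.21.
- The difference is 0.88 days, about 0.9, or 22% of the 4-day target. The arm that loses more looks better.
- At L = 40 the difference is 29.47 − 28.89 = 0.58 days. With equal loss in both arms and the same L it is zero.
- Compatibility with SD 10: the spread between lost and retained at q = 0.10 is √(0.10 × 0.90 × (45 − 28.33)²) = 5.0 days, which fits within 10.

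The documents give neither L nor q for the primary outcome.

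**The case against.** The strongest reply is that little of the primary outcome may be missing. Section {11b} says "The attending GP may exclude participants from further participation at any time for medical reasons" and lists events that end participation. A reader might infer that the sickest participants therefore drop out of the primary analysis, and that those who leave while waiting for a webinar group do too. The documents do not support this. Section {11b} concerns the allocated intervention, whereas sick days sit in the GP record and are totalled for each enrolled participant. Leaving the learning platform does not erase that record. The likelier losses are a change of GP, withdrawn consent or a GP who does not report. This objection stands, and it is why the size is left open.

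A reader might also infer that the switch inflates type I error. Under completely random loss the simulated rule held 4.9%. Freely picking the smaller p-value gave 6.1% there, but {20c} does not permit that. A general claim of inflation is not supported.

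Nor is the rule simply the wrong way round. Imputing when an at-random assumption is judged plausible is the usual direction, and imputation under that assumption was also biased under not-at-random loss (−2.8 days). The rule is incomplete on that branch, not reversed.

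Finally, imputation variables and diagnostics commonly belong in an analysis plan that is not shown. That is true of the detail. The sentence itself, however, is a stated rule, and nothing else in the article repairs it.

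**Conclusion.** The point holds as a flaw in a stated rule. The condition that selects the core model cannot be established from the data it names, has no written criterion, and is applied by analysts who are generally unblinded. Its fallback is generally not valid when loss depends on the outcome.

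The size of any bias is unknown. The figure of about 0.9 days rests wholly on assumed values (45 days among those lost, 10% against 5% loss) and would be smaller or nil if GP reporting is near complete or loss is balanced. Much larger figures may be tempting, for example with lost participants averaging 60 days, but they conflict with the protocol's SD of 10. At 12% lost the retained mean would be (30 − 7.2)/0.88 = 25.91, and the spread between the two groups alone would be √(0.12 × 0.88 × 34.09²) = 11.1. At 10% lost it would be exactly 10, leaving no other variation.

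Both analyses are already planned, so the repair settles which one is primary. It should be fixed before analysis; the design does not depend on it.

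**What to change.** - Delete the conditional sentence in {20c}.
- Fix one primary analysis in advance: all randomised participants as allocated, with multiple imputation under a stated missing-at-random assumption. Use the stratification factors, baseline data and work-ability items already collected.
- Make complete-case analysis a sensitivity analysis, and add a delta-shift (tipping-point) analysis for loss not at random.
- Confirm in {18a} and {18b} that the GP totals include participants who discontinued the intervention, subject to consent. This largely makes explicit what is already planned.

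The cost is wording and a little more analysis work. The 151 per group and the target of 600 are unchanged.
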